### Procedure

#### Baseline Assessment

Interested subjects will be sent to the designated Qualtrics platform to verify that their mobile phone number and ZIP Code are based in the United States. We will also determine human identity using a built-in CAPTCHA.

The project coordinator and/or research assistants will email each subject a one-time use personalized link. Subjects will click on the designated link taking them to a Qualtrics questionnaire. Here, they will give their informed consent and indicate whether they are over 18 years old. Thereafter, we will collect all baseline survey measures of interest as well as patient demographics. Upon survey completion, participants will be automatically enrolled onto the text messaging platform.

#### Intervention

##### Text Messages

We will send participants supportive text messages for a period of 60 days. These text messages include tips about BA and other coping skills to deal with worries and stress. The text messages used in this effort were based on core principles of evidence-based interventions for depression and anxiety and focus on rapid adoption of new behavior change strategies. Messages are balanced so that half the messages are related to BA and half are framed around other skills (see Table 2). Participants will receive one of these messages within three different time windows per day, between 9 AM and 6 PM. Participants will be sent a message asking them to rate their mood on a scale of 1 to 9, with 9 being the best mood, 3 hours after receiving the BA or skills message. These text messages were based on previous work conducted by SD and AA [23,24] and were edited by the study team members. Examples of BA and skill-based text messages are shown in Table 2.

**Table 2 table2:** Examples of StayWell at Home text messages.

Message category	Example text messages
Behavioral activation	“Make a list of people that make you happy. Commit to reaching out to at least one of them each day this week.” “If there is something you have always wanted to do, like learning to play the guitar or painting, try a YouTube video today for learning a new skill.”
Other skills and coping	“Ugh. Sheltering in place is hard. Take some time to feel angry or sad or whatever you are feeling.” “If you are feeling a bit more sad or stressed right now, you are not alone. This is a hard time, but you can do this!”

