**Methods:**

The messages were designed within two different categories: behavioral activation and coping skills. Participants will be randomized into (1) a random messaging arm, where message category and timing will be chosen with equal probabilities, and (2) a reinforcement learning arm, with a learned decision mechanism for choosing the messages. Participants in both arms will receive one message per day within three different time windows and will be asked to provide their mood rating 3 hours later. We will compare self-reported daily mood ratings; self-reported depression, using the 8-item Patient Health Questionnaire; and self-reported anxiety, using the 7-item Generalized Anxiety Disorder scale at baseline and at intervention completion.

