##### Uniform Random Policy

This study design is an MRT [16], where every day during the study treatment, allocation is characterized by a full factorial design with a total of two factors representing supportive *messages* and the *time frame* when the message was sent. The *messages* factor has two levels, and the *time frame* factor has three levels (ie, 9 AM-12 PM, 12 PM-3 PM, and 3 PM-6 PM). Each participant will be rerandomized to a new combination of *messages* and *time frame* every day. The study is set up so that each day participants will be randomized to receive one message out of the message categories (ie, BA vs other skills), constituting a multilevel MRT design with probabilities of 0.5 for the message categories and 0.33 for the timing. Thus, every participant will receive one BA or skill message per day and one mood check-in message.

This design allows us to understand the type and timings of text messages that most improve participants’ mood, which is a secondary aim of this study. MRTs enable the testing of specific intervention components, while still allowing for the evaluation of a causal, average treatment effect of the intervention [16]. Figure 2 shows our MRT design.

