##### Reinforcement Learning Policy

We employ a learned decision mechanism for the timing and type of text message. The RL algorithm learns from previous data to maximize an increase in participants’ mood using a linear regression model that is updated every morning, comparable to previous work in mobile health [25]. The learning data include which message category was previously sent and at what time, days since messages were sent, participants’ mood after the messages, and the day of the week (ie, Monday-Sunday). We employ two different learned decision mechanisms—one for the type of message and one for the timing of the message—using two separate linear regression models.

Both groups (ie, UR and RL) will receive the same messages. However, for the UR group, the type and timing of text messages will be randomly selected, whereas for the RL group, they will be selected by a learning algorithm. We will compare the effect of sending text messages by a random schedule with sending text messages chosen by the RL algorithm. This allows us to assess whether using RL to adapt the messaging scheme is more effective than a random messaging schedule. Additionally, we will be able to evaluate the effect of the individual intervention components over time, within an MRT design.

Participants in both groups can reply “STOP” or “PARAR” if they wish to stop receiving messages at any time during the study within 60 days.

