#### Secondary Analysis

For the UR intervention group, the differences in proximal outcome (ie, daily mood rating assessed 3 hours after the message sent) between both message categories (ie, BA versus coping skills) or among the time windows (ie, reference level versus the other three levels) will be examined using the weighted and centered least-squares (WCLS) method for longitudinal data analysis under the multilevel MRT design proposed by Xu et al [24]. This method is similar to the GEE approach. The independent working correlation matrix will be adopted. The covariates include days in study (ie, from 1 to 60 days), day of the week (ie, Monday-Sunday), intervention component (ie, message or time window), and the interaction term between days and intervention component. The trend of the intervention effect over days can be constant, linear, or quadratic. The message or the time window component categories will be converted to dummy variables, and each of these will be centered by the corresponding randomization probabilities (ie, 0.5 and 0.33 for each level of the message and time components, respectively).

The mood rating changes from baseline will be categorized into binary outcomes (ie, high [greater or equal to the median of the whole sample] or low [less than the median]). The WCLS estimator under the MRT design for binary outcome proposed by Qian et al [29] can be applied to the message component (ie, two-level intervention). For the timing (ie, three-level) component, we will propose the novel WCLS method by combining the ideas of both Xu et al [24] and Qian et al [29]. This method can also be extended to model the mood ratings as ordinal outcome variables. 

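### The mood rating is tied to message time, so the timing contrast cannot show which timing improves mood, and the RL–UR mood comparison can reflect when mood is rated

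*Protocol article*

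**What the plan says.** The Text Messages section places the mood prompt "3 hours after receiving the BA or skills message", and the Abstract says of both arms that participants "will be asked to provide their mood rating 3 hours later". The Uniform Random Policy section sets the message windows at "9 AM-12 PM, 12 PM-3 PM, and 3 PM-6 PM" and says that "every participant will receive one BA or skill message per day and one mood check-in message". In the UR arm, category and window are drawn with "probabilities of 0.5 for the message categories and 0.33 for the timing".

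Three uses are made of the rating:

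- **UR timing analysis.** The Secondary Analysis compares the 3-hour rating between categories "or among the time windows" by weighted and centered least squares (WCLS). Its covariates are days in study, day of week, the component, and days by component. The Uniform Random Policy section interprets the result causally: "This design allows us to understand the type and timings of text messages that most improve" mood. The Sensitivity Analysis adds a message-by-window interaction, meant to show which combination raises mood most.
- **RL policy.** The algorithm seeks to maximise mood with two regression models, one for message type and "one for the timing of the message".
- **Arm comparison.** The Primary Analysis compares RL and UR on average daily mood change from baseline by GEE.

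The Measures section names PHQ-8 and GAD-7 as primary outcomes and daily mood as secondary.

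**The concern.** Rating-prompt time equals message time plus a constant. An ordinary difference in mood between early afternoon and evening would therefore appear in the UR data as an effect of message timing. No covariate could separate the two, and no message-free day has a rating that would show the time-of-day pattern. The Limitations section concedes that any message versus no message cannot be assessed, but does not mention this problem.

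The same link reaches the arm comparison. UR ratings stay spread one third per window. The RL timing model is rewarded for moving messages, and with them ratings, to the clock time with the highest scores. Subtracting one baseline value does not undo that. At stake are the stated aim on timing, which the Discussion wants to carry into a just-in-time intervention, and the reading of an RL advantage on daily mood.

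**Working it through.** **1. The link.** Adding 3 hours to 9-12, 12-3 and 3-6 gives prompts at 12-3 PM, 3-6 PM and 6-9 PM. With one rating per day, message window and prompt window are the same three-level factor. This needs no assumption. It is exact for the prompt; replies may come later.

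**2. The plan's own sample sizes.** Per arm, n = 2(1.960 + 0.842)² [1 + 59ρ] / (60 × 0.2²).
- ρ = 0.2: 83.7, so 84.
- ρ = 0.4: 160.9, so 161. Dividing by 0.85 gives 190.

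All three match the Power Analysis section.

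**3. UR timing test, no message effect.** Suppose one rating window sits 0.1 SD from the other two, numerically the planned d = 0.1. The centred window indicators have variance 1/3 × 2/3 = 2/9, so the noncentrality is N × 60 × response rate × 0.1² × 2/9, tested on F(2, N−3).
- N = 76, full response: 10.13, rejection 80%. This agrees with the plan's 76.
- N = 107 (126 × 0.85), 70% response: 9.99, rejection 80%.

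A time-of-day difference of that size alone would be declared a timing effect about 80% of the time.

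**4. Arm comparison, no message effect.** Let the best rating window lie D above the other two, and let RL choose it with probability p. The gap is (p − 1/3)D. The standard error at 161 per arm and ρ = 0.4 is √[2 × (1 + 59 × 0.4)/(60 × 161)] = 0.0714. The documents give neither D nor p, so both are assumed.

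| D (SD) | p | Gap (SD) | False positives |
|---|---|---|---|
| 0.2 | 0.5 | 0.033 | 8% |
| 0.2 | 0.7 | 0.073 | 18% |
| 0.2 | 0.9 | 0.113 | 36% |
| 0.2 | 1.0 | 0.133 | 46% |
| 0.3 | 0.7 | 0.110 | 34% |
| 0.3 | 1.0 | 0.200 | 80% |

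If the shift is instead linear across windows, with the best window chosen half the time and the other two a quarter each, D = 0.2 gives a gap of 0.025 SD and 6%.

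**5. With an explicit learner.** This simulation used 400 runs and an illustrative rule: mostly choose the best window so far, with 10% random exploration. At D = 0.2, learning pooled over participants gave a gap of 0.096 SD and 28% rejection. Person-level learning gave 0.037 SD and 5.5%. At D = 0.4 the rates were 85% and 40%. When rating time was decoupled from message window, the gap was about 0 and rejection 4-7%.

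**6. Which adjustment works.** Here the time-of-day pattern differs between people (assumed SD 0.2 or 0.4), with no common shift, no message effect and a person-level learner (161 per arm, 60 days, 300 runs).
- A three-level window covariate leaves the gap as it was: about 0.08 and 0.21 SD, with false positives of about 19% and just over 80%.
- Weighting RL ratings by (1/3)/selection probability brings the gap to about 0.

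**The case against.** The strongest reply is that both comparisons are randomised and unbiased for what they measure. The UR contrast validly estimates the difference in 3-hour ratings between windows, and the Objective and hypotheses are largely worded as differences in mood ratings. The Discussion calls RL versus UR a comparison of two design approaches. This stands: the estimates are not invalid. What fails is reading them as a benefit of timing, or of RL, on mood.

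A second reply concerns priority. The Measures section makes mood secondary, and the Power Analysis states the primary aim as RL versus UR on depression and anxiety. This also stands. PHQ-8 and GAD-7 come from surveys not tied to message time, and the category contrast in UR is clean because window is drawn independently of category. Against it, the mood comparison appears among the primary hypotheses and under the Primary Analysis, so readers will give it weight.

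A reader might infer that RL will shift its ratings to better hours and that the mood comparison is therefore biased towards RL. The documents do not support that as a certainty. They give no time-of-day difference, and the Discussion says only that better-performing messages receive higher probabilities as responses accrue. With no time-of-day variation there is no inflation, and weak learning at a 0.2 SD common shift leaves the error rate close to 5%.

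**Conclusion.** The concern holds in two parts of different strength. That the UR timing effect cannot be separated from rating time is unconditional and follows from the text, so no later analysis detail can recover which timing improves mood most. The possible RL advantage on daily mood is conditional on mood varying by time of day and on a learner that exploits it. At an assumed common shift of 0.2 SD, 161 per arm and ρ = 0.4, the false gap runs from about 0.03 SD (6-8% false positives) to 0.13 SD (46%), against a planned effect of 0.2 SD. Matching that planned effect takes a 0.3 SD shift with full convergence.

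This should be fixed before analysis. It does not threaten the primary outcomes or the message-category result.

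**What to change.** 1. Restate the UR timing contrast as the joint difference of message time and rating time. Drop the claim that it shows which timing improves mood most, and qualify the time-of-day part of the interaction in the Sensitivity Analysis in the same way.
2. For RL versus UR daily mood, add an analysis weighting each RL rating by (1/3)/its window-selection probability, so that both arms have the UR window mix. This requires that the probabilities are stored and that every window keeps a non-zero one; the protocol states neither. If either fails, state that the unadjusted mood difference cannot be read as benefit. Do not rely on a three-level window covariate, which removes only a pattern common to everyone.
3. Rest claims of benefit for the whole RL policy on PHQ-8 and GAD-7, already the named primary outcomes.

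The messaging schedule and sample size stay as they are. The cost is wording plus one weighted analysis. That analysis loses some precision and also removes any genuine timing benefit from the mood contrast, but these data could not isolate that benefit anyway.

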##### Messaging Platform

We will use a text messaging platform, HealthySMS, developed by AA, to send text messages and manage participant responses back to our system. HealthySMS has been successfully used with various low-income, adult populations in English and Spanish [11-13].

##### Uniform Random Policy

This study design is an MRT [16], where every day during the study treatment, allocation is characterized by a full factorial design with a total of two factors representing supportive *messages* and the *time frame* when the message was sent. The *messages* factor has two levels, and the *time frame* factor has three levels (ie, 9 AM-12 PM, 12 PM-3 PM, and 3 PM-6 PM). Each participant will be rerandomized to a new combination of *messages* and *time frame* every day. The study is set up so that each day participants will be randomized to receive one message out of the message categories (ie, BA vs other skills), constituting a multilevel MRT design with probabilities of 0.5 for the message categories and 0.33 for the timing. Thus, every participant will receive one BA or skill message per day and one mood check-in message.

This design allows us to understand the type and timings of text messages that most improve participants’ mood, which is a secondary aim of this study. MRTs enable the testing of specific intervention components, while still allowing for the evaluation of a causal, average treatment effect of the intervention [16]. Figure 2 shows our MRT design.

**Figure 2 figure2:**
[figure not shown]
Microrandomized trial design of the StayWell at Home study. M: message; T: time point.

##### Reinforcement Learning Policy

We employ a learned decision mechanism for the timing and type of text message. The RL algorithm learns from previous data to maximize an increase in participants’ mood using a linear regression model that is updated every morning, comparable to previous work in mobile health [25]. The learning data include which message category was previously sent and at what time, days since messages were sent, participants’ mood after the messages, and the day of the week (ie, Monday-Sunday). We employ two different learned decision mechanisms—one for the type of message and one for the timing of the message—using two separate linear regression models.

Both groups (ie, UR and RL) will receive the same messages. However, for the UR group, the type and timing of text messages will be randomly selected, whereas for the RL group, they will be selected by a learning algorithm. We will compare the effect of sending text messages by a random schedule with sending text messages chosen by the RL algorithm. This allows us to assess whether using RL to adapt the messaging scheme is more effective than a random messaging schedule. Additionally, we will be able to evaluate the effect of the individual intervention components over time, within an MRT design.

Participants in both groups can reply “STOP” or “PARAR” if they wish to stop receiving messages at any time during the study within 60 days.

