### Primary Analysis

We hypothesize that participants will show improvements in depression symptoms, measured using the 8-item Patient Health Questionnaire (PHQ-8); anxiety symptoms, measured using the 7-item Generalized Anxiety Disorder (GAD-7) scale; and daily mood during the 60-day study. We will conduct a pre-post comparison among all participants.

We hypothesize that the participants in the group receiving RL will have a greater decrease in depressive symptoms and anxiety and a greater daily increase in mood ratings during the 60-day study than participants in the UR group (ie, randomized design).

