### Statistical Analysis Plan

#### Primary Analysis

Paired *t* tests will be used to detect the improvement in depression score (ie, PHQ-8) and anxiety score (ie, GAD-7) from baseline to follow-up measured 60 days later. Two-sample *t* tests will be used to examine the difference in improvements between the UR and RL groups. The mood ratings of each participant will be collected each day over the 60-day study period. We will also compare the average of daily mood rating improvements compared to baseline (ie, each consecutive daily measure minus the baseline measure) between these two groups using a longitudinal data analysis approach (eg, generalized estimating equation [GEE]). We will not compare the baseline characteristics between the samples in each arm. This practice could potentially be misleading because any differences would be due to chance [26-28].

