#### Sensitivity Analysis

The following sensitivity analyses will be or can be performed:

Both the primary and secondary analyses will be repeated based on the participants with at least 45 out of 60 (75%) days of data.The change of the secondary outcome will be imputed using the last-observation-carried-forward method if either the corresponding pretest or posttest value is missing.We will conduct the secondary analyses—the effects of message categories and timings—in the RL group.An interaction between the components of the message and time window can be considered in the GEE model for the secondary hypothesis. This interaction term allows us to examine what type of message, sent at what time of the day, leads to the highest increase in daily mood ratings.

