#### Secondary Analyses

Using the GEE-based sample size calculation method [31,32] with a small standardized effect size (ie, Cohen *d*=0.2), with the correlation coefficients of 0.2 and 0.4 among the daily mood rating improvements compared to baseline, sample sizes of 84 and 161 are required to detect a group effect for either the UR or RL group, respectively, randomly allocated at baseline. Assuming 15% of the participants will drop out before the end of the study, a sample size of 190 is required for each group.

At a small standardized effect size (ie, Cohen *d*=0.1), with a constant trend of intervention effect over days, sample sizes of 55 and 76 are required to detect the average daily causal effects of message and time window, respectively, for the UR intervention group, using the WCLS-based sample size calculation method proposed by Xu et al under the multilevel MRT design [33]. Assuming each participant has an expected 70% response rate to the sent messages and 15% of the participants are expected drop off before the end of the study, a sample size of 126 is recommended for the UR group. 

Since our primary aim is to detect differences between the UR and RL groups for depression and anxiety scores, we aimed to include at least 128 participants. However, since our goal is also to provide a service during this unprecedented COVID-19 pandemic, we will continue to make the program available and recruit participants until at least April 2021 or for as long as funding allows.

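### The RL arm can steer which mood prompts get answered, and the planned LOCF and 45-day sensitivity analyses would not expose a false RL mood gain from mood-dependent silence

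*Protocol article*

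**What the plan says.** - **How mood is observed.** Under Text Messages: "Participants will be sent a message asking them to rate their mood on a scale of 1 to 9". The prompt goes out 3 hours after the supportive message. No other source of post-message mood is named.
- **What RL optimises.** Under Reinforcement Learning Policy: "The RL algorithm learns from previous data to maximize an increase in participants’ mood using a linear regression model that is updated every morning". The learning data include participants' "mood after the messages, and the day of the week (ie, Monday-Sunday", together with category, time sent and days since messages. Nothing is said about a prompt that draws no reply.
- **Expected reply.** Under Power Analysis, Secondary Analyses, for sizing the UR group: "Assuming each participant has an expected 70% response rate to the sent messages".
- **The contrast.** The hypotheses expect RL to show "a greater daily increase in mood ratings during the 60-day study than participants in the UR group". The Primary Analysis states: "We will also compare the average of daily mood rating improvements compared to baseline", done "using a longitudinal data analysis approach (eg, generalized estimating equation [GEE". Measures classes daily mood as the secondary outcome, with PHQ-8 and GAD-7 primary.
- **Missing mood.** Two checks are given under Sensitivity Analysis. One is a subset: "Both the primary and secondary analyses will be repeated based on the participants with at least 45 out of 60 (75%) days of data". The other is last observation carried forward (LOCF).

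**The concern.** In an ordinary two-arm texting trial, non-response can bias a mood comparison in either direction. Here one arm's algorithm chooses the conditions under which its own outcome is observed, and it chooses them to make observed mood high.

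Suppose people in low mood are more often silent in one time window than in another. Replies from that window then look better although nobody feels better. UR spreads this selection evenly over the options. RL moves towards the flattering option, so the error favours RL.

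At stake is the claim that RL improves daily mood more than a random schedule. The two stated sensitivity analyses would be the natural place to look for the problem, and neither is built to find it.

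**Working it through.** **1. The plan's own figure.** For the RL-UR mood comparison, n per arm = 2(z₀.₉₇₅+z₀.₈₀)²[1+(m−1)ρ]/(m d²), with m=60, d=0.2 and two-sided 5%. This gives 83.7→84 at ρ=0.2 and 160.9→161 at ρ=0.4. Then 161/0.85=189.4→190. All three stated figures reproduce. At 70% reply (m=42) and ρ=0.4, n becomes 163, so non-response matters here for bias and hardly for power.

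**2. The mechanism.** Assumptions: true mood is N(0,1) in every window, no message has any effect, and reply is logistic in current mood. Slopes are log-odds per SD of mood for the three windows. They are assumed, because the documents give no mood-reply relation. The ceiling is the best window's mean answered mood minus the UR mean.

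| Slopes | Reply rates | Mean answered mood by window | UR mean | Ceiling |
|---|---|---|---|---|
| 0/0/0 | 80/70/60% | 0, 0, 0 | 0 | 0 |
| 0.5/0.5/0.5 | 70% each | 0.143 each | 0.143 | 0 |
| 0.5/0.5/0.5 | 80/70/60% | 0.096, 0.143, 0.189 | 0.138 | 0.051 |
| 0/0.25/0.5 | 70% each | 0, 0.074, 0.143 | 0.072 | 0.07 |
| 0/0.5/1 | 70% each | 0, 0.143, 0.253 | 0.132 | 0.121 |

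Different reply rates alone do nothing. Mood-dependent reply alone does nothing if it is the same in every window. The bias needs mood-dependence together with a difference between options, in slope or in rate.

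**3. Simulation on raw mood, zero true effect.** Setting: 161 per arm, 60 days, independence GEE on answered prompts with a robust SE. Two learners were tried: one mostly greedy with 10% exploration (correlation 0.4) and one using Thompson draws (correlation 0.2 and 0.4).
- 0/0.25/0.5 at 70% reply: false difference +0.04 to +0.06 SD, type I error about 10-22%.
- 0/0.5/1 at 70% reply: about +0.10 to +0.11 SD, type I error about 30-66%.
- 0.5/0.5/0.5 with 80/70/60% reply: +0.03 SD, 7% significant in RL's favour (nominal 2.5%).
- 0.4/0.5/0.6 at 70% reply: about +0.015 SD.
- Equal slopes and equal rates: 0.

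**4. The planned outcome is change from baseline.** Subtracting one baseline rating removes the stable between-person part of mood and adds the noise of that rating. Type I error falls to about 6-9% for 0/0.25/0.5, about 13-17% for 0/0.5/1, and nominal (3-4%) for 0.4/0.5/0.6. This model has its own limit. With rating = person effect + daily noise, two changes share one baseline noise term, so their correlation is σ²/(2σ²)=0.5, above the 0.2 and 0.4 used for sizing.

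**5. The stated sensitivity analyses (greedy learner, raw mood).**

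| Scenario | Main | LOCF | ≥45 days |
|---|---|---|---|
| 0/0.25/0.5, 70% | 0.052 | 0.032 | 0.146 |
| 0/0.5/1, 70% | 0.096 | 0.062 | 0.093 |
| 0.5 each, 80/70/60% | 0.034 | 0.021 | 0.281 |

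LOCF leaves about 62-65% of the false difference (0.032/0.052=62%; 0.062/0.096=65%). The subset selects on replying after randomisation and can enlarge the bias. It is also small: at 70% reply the expected count is 0.7×60=42 days, and the binomial probability of 45 or more is 24%.

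**6. Tipping point.** With 70% answered, the overall difference is 0.7D + 0.3×(RL−UR gap on unanswered prompts). It reaches zero when unanswered mood is (0.7/0.3)D = 2.33D lower in RL than in UR, which is 0.47 SD at D=0.2. If imputation first gives RL the same advantage D on unanswered prompts, the shift away from those imputed values is D+2.33D=3.33D.

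**The case against.** **Much of this is silence, and an article may be silent.** How a missing reward enters the algorithm, and how the main GEE treats missing ratings, can sit in a fuller document. This stands: that silence is not the fault raised here. The article does, however, fix two missing-data checks, and those are poorly chosen for this contrast.

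**The premise is unproven.** Nothing in the documents shows that silence depends on mood, still less that the dependence differs by window. The larger figures assume no link in one window and a strong link in another for the same people. The learner is assumed too: the article describes two separate linear regressions that also use weekday and days since messages. This stands, so the figures are illustrative.

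**Change from baseline dampens the effect.** This also stands. A reader might take the 30-66% error rates as the risk to the planned analysis. They belong to raw mood under the steepest slopes, and the planned outcome is change from baseline.

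**Reply rates would show it.** This is partly right. With equal slopes and 80/70/60% reply, simulated reply was 64% in RL against 70% in UR, and Engagement Measures already plans to explore response rates. When the windows differ in slope but not in rate, both arms stay at 70% and nothing shows.

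**Scope.** A reader might extend the worry to the depression and anxiety results. PHQ-8 and GAD-7 come from separate baseline and 60-day surveys, not from the prompts that RL optimises, so the documents do not support that.

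**Conclusion.** The concern holds as a conditional risk to one contrast: daily mood, RL against UR. It rests on the natural but unstated reading that learning and comparison both use answered prompts. It also needs mood-dependent silence whose strength, or whose accompanying reply rate, differs by window or category. Under slopes of 0/0.25/0.5 to 0/0.5/1, the false difference is about +0.04 to +0.11 SD of raw mood, against a planned d=0.2. Type I error is about 6-17% on the planned change from baseline. With similar slopes and reply rates the bias is negligible.

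The documents do not show that an RL mood gain would be false, and they do not make the GEE unsuitable as the main analysis. The firm part is narrower: neither LOCF nor the 45-day subset addresses mood-dependent silence, and the subset can make matters worse. Limitations does not mention the issue.

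**What to change.** Keep the GEE as the main analysis and leave the algorithm unchanged. Under Sensitivity Analysis, for the RL-UR mood contrast only:

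1. Replace LOCF and the 45-of-60-day subset with multiple imputation over every scheduled day 1-60 of every randomised participant, including days after a STOP reply. Use window, category, study day, earlier ratings, and baseline PHQ-8 and GAD-7.
2. Add a pre-specified delta shift for unanswered prompts, by arm. This step is needed. In simulation, reply weights based on window and past ratings, or an exchangeable working correlation, removed only about 12-48% of the false difference.
3. Report the tipping point (an RL-UR gap in unanswered mood of about 2.3 times the observed difference at 70% reply) and say whether it is measured as that gap or as a shift from the imputed values.
4. Report reply rates by arm, window and category, and interpret any RL mood advantage in that light.
5. State how unanswered prompts enter the learning data and the main GEE.

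The cost is analysis-plan wording and some programming on data already logged, with no extra participants or procedures. The downside is a possibly less favourable reading of the RL mood result.
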